### **SAEs will be reported to:**

#### **University Health Network**

Attention: [name] RN, MHM, BScN, CHE, CCRP  
Clinical Research Nurse Manager & Project Manager

University Health Network/Toronto General Hospital  
[name]  
[name]

[contact] [name]  
[contact]  
Email: [[contact]](mailto:[contact])

Study medication will be discontinued in the following instances: unacceptable toxicity, or toxicity that, in the judgment of the investigator, compromises the ability to continue study-specific procedures or is considered to not be in the subject's best interest.

## 11.0 STATISTICAL CONSIDERATIONS

### 11.1 General Study Design

*This is a double-blinded, individually randomized, parallel-group randomized placebo controlled clinical trial.*

### 11.2 Sample Size Considerations/Justification

The 3-month risk of infection in healthcare workers not treated with prophylaxis was assumed to be 10%. This corresponds to a hazard of 0.035 infections per month under the assumption of exponentially-distributed time to infection. Reducing 3-month risk to ~6% was judged to be both feasible and clinically important; this reduction corresponds to a hazard ratio of 0.588. With a one-sided type I error rate of 5%, to have 80% power, to detect this hazard ratio, a total of 92 events are needed. Using the event rates above and exactly 3 months + 14 days planned follow-up for each participant, a total of 988 participants need to be randomized. These calculations account for the single interim analysis described below.

### 11.3 Endpoints/Outcome Measures

#### 11.3.1 Analysis of Primary Outcome Measures

The primary outcome comprises a microbiologically confirmed COVID-19 infection and the date of the confirmatory test. At the date of an analysis (interim or final), each participant will have either an infection and date of infection, or a known uninfected status and time since randomization (censoring date). The rates of the outcome will be

compared between randomized groups using a Cox proportional hazards model with stratification by site (used in the stratified randomization) and inclusion of job class as a covariate. As there are too many distinct job classes in the inclusion criteria for them all to be included in the model, they will be grouped before any analysis begins. The grouping will combine classes of job deemed to be at similar levels of exposure, while keeping groups a reasonable size. If there is heterogeneity in risk by job class, inclusion of this factor in the analyses increases power with compromising type I error. See section 9.5 for details on inference at the interim and final analyses. A plot of cumulative incidence of infection over the 104-day study period will be made for each group and the overall rates of infection in each study arm will be calculated. All primary analyses will be by intention-to-treat. While loss to follow-up is expected to be low, if more than 5% of participants withdraw, missing data will be imputed under a variety of assumptions, to assess the robustness of our findings.

### 11.3.2 Analysis of Secondary Outcome Measures

**Adverse events** will be tabulated by study arm. The percentages of participants experiencing each type of AE, or any AE will be calculated by severity level. The rate per 100 person-days will also be calculated by AE and severity level. If warranted, AEs will be compared between groups using the methods for the primary analysis. **Symptom duration, duration of hospitalization due to COVID-19 disease, days of respiratory failure requiring ventilatory support attributable, and number of days ineligible/unable to work due to COVID-19** will be summarized within group by the median and interquartile range as well as the mean. As the majority of participants will have zero for all of these outcomes, a bootstrap hypothesis test, with stratification by site, will be used to test the hypothesis of no treatment effect. A 95% confidence interval for the mean difference in days will also be computed using the bootstrap. Mortality is expected to be very low, so will simply be summarized by a count and percentage in each arm. The relative risk of mortality by 90 days will be calculated if feasible. **Seropositivity** will be analyzed by the same approach described for the primary outcome. **Short-term psychological impact of exposure to COVID-19** as measured by the K10 will be summarized by group at each of the three time points (day 1, 60, and 120), using the mean and standard deviation as well as the percentages with scores at or above the standard cutoff score of 16. As the trial is blinded, there is no expectation of a direct effect of treatment on the K10. Those who become infected may have higher scores, so results will also be presented according to the previous occurrence of an infection. The primary comparison of this outcome will use a linear model to estimate the effect on 60-day values of site, study arm, and job class, using the day 1 value as a covariate. The relative risks of exceeding the threshold at 60 days for these same variables will be estimated in a log-binomial model with the same covariate. The change in K10 between days 60 and 120

will be estimated to assess whether there is a reduction in psychological impact once participants know they are on prophylaxis with an active drug.

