## 2.0 STUDY OBJECTIVES AND DESIGN

### 2.1 Overall Study Design

The HEROS study is a double-blind, randomized placebo controlled trial of oral HCQ 400 mg taken once daily for three months as PrEP to prevent COVID-19 in front line health care workers at high risk for SARS-CoV-2 exposure.

The trial will recruit 988 HCW at high risk of COVID-19 exposure from five academic hospitals in downtown Toronto: University Health Network (UHN) [Toronto General Hospital (TGH) / Toronto Western Hospital (TWH)], St. Michael's Hospital (SMH), Sinai Health System (SHS), and Sunnybrook Health Sciences Centre (SHSC).

Within each site, participants will be randomly assigned to either the intervention arm with HCQ or the placebo arm using a fixed 1:1 allocation ratio produced by a computer-based random number generator using variable block sizes to ensure equal allocation to each group.

The rationale for conducting a randomized placebo-controlled trial is:

*first*, little is known to date regarding the effectiveness of HCQ against SARS-CoV-2 *in vivo*, yet *in vitro* studies signal plausibility of virucidal activity;

*second*, no data exist supporting the efficacy of any biomedical interventions in health care workers for preventing COVID-19.

Participants will be seen at baseline, and then undergo monthly follow-up at day 30, 60, and 90, 120. The primary outcome will be symptomatic COVID-19 (with microbiological confirmation of SARS-COV-2 infection) anytime within 104 days (= the 90 days of the randomization period plus 14 additional days to allow for viral incubation, delayed symptom onset and/or seroconversion).

At 90 days an open label extension wherein all participants are offered a one-month course of HCQ 400mg once daily for PrEP of COVID-19. The rationale for the open-label extension is that it will improve participant adherence to their allocation group during the randomization period. It will further allow additional evidence regarding adherence and safety. A period of one month will be offered as this is the amount of drug that is available for the study.

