### **Secondary outcomes measures are:**

- a) **Adverse events:** as defined using the DAIDS Table for Grading the Severity of Adverse Events, until day 120^27
- b) **Symptom duration of COVID-19:** measured in days.
- c) **Days of hospitalization attributable to COVID-19:** The number of days (or partial days) spent admitted to an acute care hospital during the study period.

- d) **Respiratory failure requiring ventilatory support attributable to COVID-19:** The number of days (or partial days) requiring i) non-invasive and ii) endotracheal intubation with ventilation during the study period.
- e) **Mortality** attributable to COVID-19 and all-cause mortality during the study period.
- f) **Number of days ineligible/unable to work due to COVID-19:** measured from symptom onset to return to work date.
- g) **Seropositivity:** reactive serology by day 120.
- h) **Short-term psychological impact of exposure to COVID-19** will be measured at the beginning of randomization (day 1), during the randomized period (day 60) and during the open-label period (day 120) using the K10, a validated measure of non-specific psychological distress, with a standard cutoff score of  $\geq 16$ .

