## 6.8 Participant Access to Study Medication at Study Closure

At the end of the 90-day randomization period, all participants will be offered a 30-day open-label extension of hydroxychloroquine 400 mg orally daily. Beyond the study period, HCQ is not currently indicated for routine prophylaxis of viral infections. If the study is terminated for efficacy, all participants will be offered the 30-day open-label extension at that time.

In the event that a study participant tests positive for COVID-19, participants will be instructed to stop their study drug. If this occurs during the randomization period, neither participant nor study staff will not be unblinded to allocation group. Efforts will be made to link the individual to ongoing clinical trials of COVID-19 treatment if such trials are enrolling in proximity to the study site and the participant meets the inclusion criteria. However, no guarantees of access to investigational product can be made. At the time of writing, there are no known effective treatments for established COVID-19 infection.

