## Special Schedule Considerations:

**If any participant is under quarantine for suspected COVID-19 (ie they are awaiting confirmatory testing results) and, therefore, unable to make a study visit in a visit window,** a remote visit will occur and every effort will be made to have an in-person study visit scheduled as soon as they are cleared as negative for COVID-19 for sample collection.

**If any participant is confirmed COVID-19 positive during the study, the above scheduled visits will continue *remotely* (telephone) and the weekly email questionnaire will continue.** During the time in which they are symptomatic and under isolation, the following events will be suspended: dispensation of drug, self-collected viral detection sample, venous blood draw. COVID-19 positive participants who have recovered and have been deemed safe to return to work by their institution will be asked to return to the above study schedule.

**COVID-19 positive participants who have been deemed safe to return to work will be given the option of either a) resuming their blinded study drug and then entering the open-label extension at day 90 as previously scheduled, or b) starting the 30-day open-label extension immediately.** The rationale for providing the option to resume blinded study drug is that it remains unknown whether individuals who recover from COVID-19 infection remain susceptible to re-infection, and acquiring COVID-19 does not necessarily mean that the blinded study drug that the participant had been using was not providing partial protection. The rationale for providing the option to skip immediately to the open-label extension is that some participants may understandably prefer to abandon their study drug under these circumstances, and the study has committed to providing every participant with a one-month open-label extension.

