# 10.0 EVALUATION and REPORTING OF ADVERSE EVENTS

## 10.1 Adverse Event Reporting

Toxicities will be graded on a 4-point scale according to standard guidelines outlined in the “Division of AIDS Table for Grading the Severity of Adult and Pediatric Adverse Events”. In general, grade 1 and 2 events will not be considered adverse events, but details should be documented in the source documents. Stable chronic conditions which are present prior to clinical study entry and do not worsen are not considered adverse events and will be accounted for in the participant’s medical history. Participants who have an adverse event (AE) should be followed and treated by the site Investigator until the abnormal parameter or symptom has resolved or stabilized. It is up to the clinician to determine that the AE is either resolved or that it has reached a stable state, after which no further follow-up is necessary. There should also be source documentation to support this determination.

At each contact with the participant, information regarding adverse events will be elicited by appropriate questioning and examinations, and will be recorded immediately on a source document (e.g., progress notes, laboratory reports, survey tools, and data collection tools). The start date, stop date, severity of each reportable event, and the PI's judgment of the AE's relationship to the study medication/intervention will also be recorded.

The Investigator or designee must report any severe adverse event (SAE) occurring in a participant receiving study drug to the Sponsor within 24 hours, even if the SAE is not drug-related. This should be done by telephone and by sending a faxed or emailed copy of the Serious Adverse Event form plus other supporting documentation, as required. All additional follow-up evaluations must also be reported as soon as possible in the same manner. All SAEs will be followed until the Investigator agrees that the event is satisfactorily resolved, becomes chronic, or that no further follow-up is required.

A Serious Adverse Event is defined as an AE meeting one of the following:

- Death during the period of protocol-defined surveillance
- Life Threatening Event (immediate risk of death at the time of the event)
- In-patient hospitalization or prolongation of existing hospitalization during the period of protocol-defined surveillance
- Results in congenital anomaly or birth defect
- Results in a persistent or significant disability/incapacity

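### Adverse-event tables by study arm run to Day 120 without a cut where open-label HCQ starts, so up to 25% of placebo-arm person-days are on HCQ and any HCQ excess is diluted

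*Protocol*

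**What the plan says.** Section 2.4 of the protocol defines the adverse-event outcome "as defined using the DAIDS Table for Grading the Severity of Adverse Events, until day 120".

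Section 11.3.2 says of these events that they "will be tabulated by study arm. The percentages of participants experiencing each type of AE, or any AE will be calculated by severity level". It continues: "The rate per 100 person-days will also be calculated by AE and severity level". A between-arm comparison is optional: "If warranted, AEs will be compared between groups using the methods for the primary analysis". Neither the tables nor the comparison is split by treatment period.

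Section 6.8 states: "At the end of the 90-day randomization period, all participants will be offered a 30-day open-label extension of hydroxychloroquine 400 mg orally daily". Recovered infected participants can start sooner. Under the special schedule considerations in section 9.1 they choose between resuming blinded drug and "entering the open-label extension at day 90 as previously scheduled, or b) starting the 30-day open-label extension immediately".

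Section 2.1 gives safety evidence as one purpose of the extension: "It will further allow additional evidence regarding adherence and safety". Adverse events are assessed at Days 30, 60, 90 and 120 (Table 1).

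Section 10.1 narrows what counts: "In general, grade 1 and 2 events will not be considered adverse events, but details should be documented in the source documents".

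**The concern.** The randomised contrast, HCQ against placebo, exists only while the placebo arm is off HCQ. From Day 90 both arms may take the same drug. A table by randomised arm to Day 120 therefore adds HCQ events and HCQ person-days to the placebo column, and the two arms move together whenever HCQ raises the event rate.

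The direction is unfavourable for a safety analysis, because part of a real excess is hidden. The participants are healthy workers taking a preventive drug, so an understated harm matters. The extra month does not pay for itself with more data: it adds events to both arms but weakens the contrast. The tables described also never show the open-label month by itself, although safety evidence is one stated reason for having it.

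Elsewhere section 11.3.2 does set time limits or recognise the switch. The mortality relative risk is taken at 90 days, and the Day 60 to Day 120 change in K10 is examined because participants then know that they are on active drug. The adverse-event text does neither.

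**Working it through.** **Inputs from the protocol.** 988 participants randomised 1:1, so 494 per arm. Blinded period 90 days, open-label period 30 days, adverse events to Day 120. The primary analysis follows to Day 104 (90 + 14). Control infection risk is 10% at 3 months, with HR 0.588.

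**Assumptions, since the protocol gives no figure.** True adverse-event rate ratio R on HCQ; constant rates that follow the drug currently taken; a share u of each arm takes the extension. No stated adverse-event figure exists to reproduce. The infection hazard used below does reproduce: −ln(0.9)/3 = 0.0351 per month, against 0.035 in section 11.2.

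**Share of placebo-arm time on HCQ.** At full uptake 494 × 30 = 14,820 of 494 × 120 = 59,280 person-days, or 25%. At half uptake it is 12.5%.

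**Ratio seen when follow-up is pooled to day T.** In units of the off-drug rate, expected events per participant are:

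- HCQ arm: (90 + u(T − 90))R + (1 − u)(T − 90)
- placebo arm: 90 + (1 − u)(T − 90) + u(T − 90)R

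| Window | Uptake | R = 2 | Ratio seen |
|---|---|---|---|
| Day 90 | – | 180/90 | 2.00 |
| Day 104 | half | 201/111 | 1.81 |
| Day 104 | full | 208/118 | 1.76 |
| Day 120 | half | 225/135 | 1.67 |
| Day 120 | full | 240/150 | 1.60 |

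At Day 120 with full uptake, true ratios of 1.5 and 3 show as 1.33 and 2.00. The absolute rate difference is 75% of its true value (90/120).

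The percentage tables behave in the same way. An assumed 10% against 5% at Day 90 (ratio 2.0) becomes 13.1% against 8.3% at Day 120 with full uptake (ratio 1.58). If instead the whole excess arises on starting HCQ, the Day 120 ratio of percentages is 1.27 at half uptake and 1.0 at full uptake.

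**Early switching alone, cut at Day 90.** Suppose every infected participant switches early, g days after infection. HCQ days in the placebo arm are 494 × ∫ f(t) min(30, 90 − t − g) dt, where f is the exponential infection density. With s as their share of 494 × 90 = 44,460 person-days, the ratio seen is R/((1 − s) + sR).

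| g (days) | HCQ days | s | Ratio seen (R = 2) |
|---|---|---|---|
| 10 | 1,070 | 2.4% | 1.95 |
| 14 | 1,006 | 2.3% | 1.96 |
| 28 | 782 | 1.8% | 1.97 |

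**Illustrative power, R = 2, two-sided 5%.** With expected events E1 (HCQ) and E0 (placebo), z = ln(E1/E0)/√(1/E1 + 1/E0) and power = Φ(z − 1.96). At an assumed 5 events per 100 placebo participants in 90 days:

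- Day 90: 49.4 and 24.7, z = 2.81, power 80%
- Day 104, full uptake: 57.1 and 32.4, z = 2.58, power 73%
- Day 120, full uptake: 65.9 and 41.2, z = 2.37, power 66%

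For 3 per 100 the powers are 59%, 51% and 45%; for 10 per 100 they are 98%, 95% and 92%.

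**Where the cut must fall.** Cutting only at the first open-label tablet leaves those who decline the extension uncut, so their off-drug days to Day 120 stay in their arm. At half uptake and R = 2 the HCQ arm has 180 + 0.5 × 30 = 195 and the placebo arm 90 + 0.5 × 30 = 105, over equal person-time: 195/105 = 1.86. Ending everyone's count no later than the Day 90 visit removes this.

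**The case against.** The strongest reply is that nothing orders pooling across Day 90. Section 2.4 sets the follow-up of the outcome, section 11.3.2 sets the grouping, and a split by treatment period is often left to the SAP. The two periods are also described apart: section 6.5 ties placebo to the 90-day period and gives the extension to all participants. This carries some weight, since an SAP could add a split. But the protocol does state both the window and the grouping, and nothing in it limits the tables to the blinded period. An SAP that followed both statements literally would mix the periods.

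Second, the only between-arm comparison is optional and borrows the primary methods, so its window may be 104 days. That stands for the comparison, and the milder figures of 1.76 to 1.81 belong beside the Day 120 ones. It does not cover the tables, and 104 days still includes 14 open-label days.

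Third, the power figures rest on event rates with no source and on a test that the protocol does not plan. That also stands. At 1 event per 100 the same formula gives about 24% at Day 90 and 18% at Day 120, uninformative either way.

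A reader might infer that the harm signal is lost or that participants are left unprotected. The documents do not support this. Start and stop dates of events are recorded and serious events are reported within 24 hours (section 10.1), and the DSMB reviews safety (section 7.3). A reader might also carry the early-switch option over to the primary analysis, but that option begins after the primary event has occurred.

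**Conclusion.** The point holds, as a minor one. Read literally, sections 2.4 and 11.3.2 put up to 25% of placebo-arm person-days on HCQ and bias the safety contrast towards no difference. The direction is certain if HCQ raises the event rate and some placebo participants take the extension.

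The size is not certain, because it depends on uptake and on how the event rate behaves over time. Under constant rates a true ratio of 2 shows as 1.60 to 1.67 at Day 120, or 1.76 to 1.81 at Day 104. Mainly grade 3 and 4 events are concerned, given the counting rule in section 10.1. Early switching is a small addition, and the powers only illustrate that a longer pooled window weakens the comparison.

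**What to change.** Add to section 11.3.2: between-arm adverse-event tables, and any comparison, count events and person-days up to the earlier of the Day 90 visit (end of the blinded period) and the first open-label tablet, for all participants including those who decline the extension. Report later events separately as open-label, by original arm and with their own person-days. Keep the full Day 120 table by randomised arm as a supplement.

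The cost is one sentence and one recorded date, the first open-label tablet. No visit is added.

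There are two downsides. The main comparison gives up the Day 90 to 120 person-time. Early switchers are also cut at a point that depends on a post-randomisation infection. If all who can switch do so 14 days after infection, that is about 41 participants on placebo and 25 on HCQ at HR 0.588. The placebo person-days lost before Day 90 are 1,769, 1,599 or 1,070 for g = 10, 14 or 28, that is 4.0%, 3.6% or 2.4% of 44,460. The supplementary table covers this loss.

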### 11.3.3 Interim Analysis

One interim analysis of the primary outcome is planned when half the expected number of events (46/92) has occurred. The table below shows the properties of this design. At the first interim analysis, a Z-statistic ( $-\log(\text{HR})/(\text{Standard Error})$ ) larger than 2.67 will be taken as evidence of efficacy; this is the same as checking whether the one-sided p-value is  $< 0.0038$ . If the true hazard ratio is 0.588 (as in the sample size calculation), there is a 19% chance of stopping for efficacy at this interim analysis. The trial may stop for futility (with the recommendation coming from the DSMC, as this is a non-binding futility boundary) if the Z-statistic is less than -0.01, which corresponds to the one-sided p-value being  $> 0.51$ . If the true HR is 1.0, there is a 49% chance that the interim analysis will cross this futility boundary. If the trial does not stop for futility or efficacy, the final analysis will take place at the earlier of the date that all participants have reached the end of the 104-day randomized or when 92 events have occurred. This final analysis will declare superiority of HCQ over placebo if the Z-statistic is  $> 1.65$  (or the one-sided p-value is  $< 0.049$ ). With 92 total events, power is 80% against  $\text{HR}=0.588$  and type I error is 5% across the whole trial. One-sided testing is justified here to increase power, as there is no interest in concluding that HCQ is inferior to placebo. A finding other than HCQ being superior will lead to the same decision not to use it.

| Analysis   | Value                        | Efficacy | Futility |
|------------|------------------------------|----------|----------|
| IA 1: 50%  | Z                            | 2.6700   | -0.0142  |
| N: 988     | p (1-sided)                  | 0.0038   | 0.5057   |
| Events: 46 | HR at bound                  | 0.4542   | 1.0042   |
| Month: 1.7 | P(Cross) if $\text{HR}=1$    | 0.0038   | 0.4943   |
|            | P(Cross) if $\text{HR}=0.59$ | 0.1864   | 0.0365   |
| Final      | Z                            | 1.6549   | 1.6549   |
| N: 988     | p (1-sided)                  | 0.0490   | 0.0490   |
| Events: 92 | HR at bound                  | 0.7076   | 0.7076   |
| Month: 3.5 | P(Cross) if $\text{HR}=1$    | 0.0489   | 0.9511   |
|            | P(Cross) if $\text{HR}=0.59$ | 0.8000   | 0.2000   |

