At the final analysis, the hazard ratio, its 90.2% confidence interval will be calculated, as the upper limit of the 90.2% CI will lie below 1 if the null hypothesis that HR=1 is rejected.

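### Section 11.3.2 sends any adverse-event comparison to the primary-analysis methods, whose only stated test is one-sided for HCQ benefit and so cannot declare an excess of adverse events

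*Protocol*

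**What the plan says.** Section 2.3 lists adverse events first among the secondary outcomes to be compared between arms. Section 11.3.2 plans a descriptive analysis whatever the data show: percentages by type and severity in each arm, and also "The rate per 100 person-days will also be calculated by AE and severity level". It then adds a conditional comparison: "If warranted, AEs will be compared between groups using the methods for the primary analysis".

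The primary methods begin in section 11.3.1. Infection rates are "compared between randomized groups using a Cox proportional hazards model with stratification by site", with job class as a covariate. For inference the section points onward: "See section 9.5 for details on inference at the interim and final analyses". Section 9.5 is the weekly questionnaire, so that pointer is wrong. The rules for the interim and final analyses are in section 11.3.3, and the one-sided 5% error rate is in section 11.2.

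Those rules run in one direction. Z is defined as -log(HR)/SE, and superiority is declared at the final analysis if Z exceeds 1.65 (one-sided p below 0.049). The reason given is: "One-sided testing is justified here to increase power, as there is no interest in concluding that HCQ is inferior to placebo". The 90.2% interval is chosen to match, because "the upper limit of the 90.2% CI will lie below 1 if the null hypothesis that HR=1 is rejected".

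No direction, significance level or interval level is stated for AEs.

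**The concern.** The argument for one-sided testing is about infection: if HCQ does not prevent it, the decision is the same whether HCQ is neutral or worse. For AEs the direction of interest is reversed. If HCQ did prevent infection, an excess of AEs is the finding that could still change the decision to use it.

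The protocol itself expects the difference to go that way. Sections 1.3 and 6.1.2 list side effects of HCQ, and section 6.3.1 expects none from placebo.

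Carried over as written, the primary rule turns an excess on HCQ into a negative Z and a one-sided p near 1, which would formally be reported as non-significant. At stake is how a safety comparison would be reported in a trial of a preventive drug.

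**Working it through.** **1. Is the primary method one-sided for benefit?** Inputs: hazard ratio 0.588, one-sided alpha 5%, power 80% and 92 events (section 11.2); boundaries 2.67, -0.0142 and 1.6549 at 46 and 92 events (section 11.3.3).

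- Freedman, one-sided: (1.645 + 0.842)² × ((1 + 0.588)/(1 - 0.588))² = 6.18 × 14.86 ≈ 92 events, the plan's figure.
- Schoenfeld: 4 × 6.18/(ln 0.588)² gives 88 events one-sided. The two-sided version needs 112. The design is therefore one-sided.
- Bivariate normal check of the boundaries: type I error 0.0489 with futility stopping (plan: 0.0489) and 0.0500 ignoring it. Power is 0.809 (plan: 0.80).
- 1 - Φ(1.6549) = 0.0490, and 1 - 2 × 0.0490 = 0.902. This is where the 90.2% interval comes from.

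The plan's primary figures agree with one another as a one-sided design.

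**2. What does that rule do for AEs?** It rejects only when Z exceeds 1.6549, that is, when the estimated hazard ratio (HCQ vs placebo) is clearly below 1. No value of Z leads to a declaration of excess, so the chance of declaring one is zero whatever the true hazard ratio.

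**3. How does a two-sided test compare?** The protocol gives no AE rates by arm, so the event counts and hazard ratios here are assumptions. With E participants having an event and 1:1 allocation, the mean of Z is μ = -ln(HR) × √E/2. Then:

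- chance that the primary rule rejects (a false claim of fewer AEs) = 1 - Φ(1.6549 - μ)
- chance that a two-sided 5% test declares an excess = Φ(-1.96 - μ)
- chance that the lower 90.2% limit lies above 1 = Φ(-1.6549 - μ)

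Example with E = 92 and HR 1.5: μ = -0.4055 × 9.592/2 = -1.94. The two-sided chance is Φ(-0.015) = 49%.

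| HR | Events | Primary rule rejects (falsely, for fewer AEs) | Two-sided 5% test declares excess | Lower 90.2% limit above 1 |
|---|---|---|---|---|
| 1.5 | 50 | 0.10% | 30% | 41% |
| 1.5 | 92 | 0.016% | 49% | 61% |
| 1.5 | 200 | <0.001% | 82% | 89% |
| 1.5 | 300 | <0.001% | 94% | 97% |
| 2.0 | 50 | 0.002% | 69% | 79% |
| 2.0 | 92 | <0.001% | 91% | 95% |
| 2.0 | 200 | <0.001% | 99.8% | 99.9% |
| 2.0 | 300 | <0.001% | about 100% | about 100% |

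**4. The same check on the risk scale.** Assume 494 per arm (988/2), H = -ln(1 - p), and expected Z = -ln(H1/H0)/√(1/(494·p0) + 1/(494·p1)).

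- 5% on placebo vs 10% on HCQ: -0.720/0.246 = -2.92; two-sided power 83%.
- 2% vs 5%: -0.932/0.376 = -2.48; two-sided power 70%.

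At these expected values the one-sided p for benefit is 0.998 and 0.993.

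**The case against.** The strongest reply is that the primary-analysis methods may mean only the Cox model of section 11.3.1. The one-sided rule sits under the interim-analysis heading, is written for the primary outcome, and has cut-offs tied to 46 and 92 infections. In section 11.3.2 the day-count outcomes are tested for no treatment effect with a 95% interval, so the authors did not apply one-sided inference everywhere. This reading is reasonable, but it does not remove the point. Section 11.3.1 sends the reader onward for inference, section 11.3.3 holds the only decision rule for that analysis, and nothing exempts AEs. If only the model is meant, the direction and level for AEs are undefined in a comparison that is made only if warranted.

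A reader might infer that an excess of AEs could never come to light, or that the risk-benefit conclusion would be wrong. The documents do not support that. AEs are tabulated by arm regardless of any test, the hazard ratio comes with an interval whose lower limit can lie above 1, and under section 7.3 an independent DSMB reviews safety. No stated decision depends on an AE p-value.

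It is also fair to say that the AE rates used above are assumed. Section 10.1 generally does not count grade 1 and 2 events as adverse events, so the common side effects listed in section 6.1.2 are no guide to the number of events that would be compared.

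**Conclusion.** The concern holds in a limited form. Read as written, section 11.3.2 applies to AEs a test that can reject only in favour of HCQ, on a rationale that does not suit safety. An excess cannot be declared by that test. With an assumed 92 AE events, a two-sided 5% test would declare an excess with about 49% power at a hazard ratio of 1.5 and about 91% at 2.0, against zero for the stated rule.

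The zero follows from the rule itself. The comparison figures rest on assumed event counts and hazard ratios, 1:1 allocation and the usual normal approximation for the log hazard ratio.

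The severity is moderate. The cross-reference is unsuited to its endpoint, but the primary result is unaffected and the other safety information in the plan could still show harm.

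**What to change.** Replace the sentence in section 11.3.2 with:

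> AEs will be compared between groups with the site-stratified Cox model used for the primary outcome, reporting the hazard ratio (HCQ vs placebo) with a two-sided 95% confidence interval and, where tested, a two-sided 5% test; the one-sided rule and 90.2% interval of 11.3.3 apply to the primary efficacy outcome only.

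Reporting estimates with two-sided intervals and no AE test would also resolve the point. While editing, correct the pointer in section 11.3.1 from 9.5 to 11.3.3.

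The cost is one sentence and one cross-reference. No extra data or participants are needed, and N = 988, the 92 events and the primary alpha stay as they are. The change is best made before any unblinded AE data are seen.
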